## Abstract

**Background:**

The adoption of a healthy lifestyle, including physical activity, a balanced diet, a moderate alcohol consumption and abstinence from smoking, are associated with large decreases in the incidence and mortality rates for the most common chronic diseases. That is why primary health care (PHC) services are trying, so far with less success than desirable, to promote healthy lifestyles among patients. The objective of this study is to design and model, under a participative collaboration framework between clinicians and researchers, interventions that are feasible and sustainable for the promotion of healthy lifestyles in PHC.

**Methods and design:**

Phase I formative research and a quasi-experimental evaluation of the modelling and planning process will be undertaken in eight primary care centres (PCCs) of the Basque Health Service – OSAKIDETZA, of which four centres will be assigned for convenience to the Intervention Group (the others being Controls). Twelve structured study, discussion and consensus sessions supported by reviews of the literature and relevant documents, will be undertaken throughout 12 months. The first four sessions, including a descriptive strategic needs assessment, will lead to the prioritisation of a health promotion aim in each centre. In the remaining eight sessions, collaborative design of intervention strategies, on the basis of a planning process and pilot trials, will be carried out. The impact of the formative process on the practice of healthy lifestyle promotion, attitude towards health promotion and other factors associated with the optimisation of preventive clinical practice will be assessed, through pre- and post-programme evaluations and comparisons of the indicators measured in professionals from the centres assigned to the Intervention or Control Groups.

**Discussion:**

There are four necessary factors for the outcome to be successful and result in important changes: (1) the commitment of professional and community partners who are involved; (2) their competence for change; (3) the active cooperation and participation of the interdisciplinary partners involved throughout the process of change; and (4) the availability of resources necessary to facilitate the change.

## Background

Although it is well known that the most common chronic diseases are caused by unhealthy behaviours such as smoking and drinking alcohol, a sedentary lifestyle and an unbalanced diet; in spite of primary health care (PHC) services having many opportunities to intervene in those lifestyles; and despite the fact that its professionals are convinced that healthy lifestyle promotion by health services has a potential impact that few other interventions could match; the truth is that healthy lifestyle promotion is far from being an integrated element of clinical practice in PHC [1]. The two main reasons for this are: a) insufficient evidence of the effect of interventions and active components on multiple risk behaviours [2,3]; and b) the difficulties in changing existing practice to include innovative interventions under real-world conditions [4,5].

To date, interventions on lifestyle modification in PHC have shown mixed results [2,3]. There is solid evidence proving the effectiveness of brief advice given in PHC in achieving smoking cessation and reductions in alcohol consumption [6-8]. In the case of physical activity, general advice has little effects, while, medical guidance in the form of a written prescription for physical activity results in small or moderate changes even in the long term [9,10]. However, concerning diet and the simultaneous approach of several behavioural risk factors, there is still insufficient evidence on the effectiveness of the advice given in PHC [11-13]. Even for those lifestyles for which there is evidence of effectiveness, it is not clear which are the effective components of the interventions, and there is high heterogeneity across the results obtained depending on the context and the way in which the interventions are implemented [3].

Changing people's lifestyles is not easy, because their behaviour is determined by many personal, institutional and environmental factors, which operate and interact at individual, interpersonal and community levels [14]. Consequently, there is a growing recognition of the need to base lifestyle change interventions on relevant behaviour change theories and to follow a suitable process linking intervention techniques and strategies with this theory. This, as well as producing more effective interventions, should make it possible to identify which factors work, how they work and why [15]. Classical planning models such as Precede-Proceed [16] or more modern ones such as Intervention Mapping and Causal Modelling [17,18], as well as consensus techniques and constructs of behaviour change [19] and guidelines such as those of NICE concerning the development of behaviour change interventions [20], could facilitate this process of mapping and evaluation of theories and effective techniques.

The improvement of preventive clinical practice involves the transferring and dissemination of effective and efficient interventions to real-world clinical conditions [21]. The failure to date in translating identified effective clinical interventions into routine practice represents the gap between what is avoidable or preventable via these interventions and what is achieved in practice. Several types of quality improvement interventions have been developed with the objective of reducing this gap. In general, what has been recommended is the use of multifaceted interventions that include several strategies such audits and feedback, external facilitators, evidence-based educational meetings with active participation and knowledge management. Specifically, in the area of optimisation of prevention services, efficient registration and reminding systems, a revision of professionals' roles, nursing-based programmes, the creation of multidisciplinary teams, integrated care services and collaboration with community resources, have shown positive results [22-34].

However, the evidence on translation of effective preventive interventions, strategies and programmes is at present insufficient or not conclusive [35]. On the one hand, the effectiveness of the majority of these strategies is low or moderate with a high variation in the degree of change achieved. On the other hand, interventions that have had some success are not easily incorporable to the real-world context of health centres [36]. This is why it has been recommended that interventions for the optimisation of preventive clinical practice should be adapted to the real context of each centre and health system: to their needs, characteristics and identified barriers [37-39]. In line with this, recent models concerning translation of evidence into practice propose the optimisation of clinical practice through research [40-42]. Under this framework, research should be used to optimise practice instead of using the practice context to attempt to demonstrate the relevance of previous studies. Interventions should be designed in the same context in which they are going to be executed, with the active participation of the principle players [41].

There are many challenges in the design, evaluation and transfer of healthy lifestyle promotion to the clinical context, mainly due to the complexity of the interventions [43-45]. They are composed of a large number of elements and are focussed on a variety of interrelated levels: the patient as an individual, health professionals and the organisation that offers health services to the community, in a context that is characterised by work overload and lack of time. In 2000, the Medical Research Council (MRC) of the United Kingdom defined a theoretical and methodological framework for the design and evaluation of this type of complex interventions in the clinical context [43]. This framework, updated in 2008 [45], uses simultaneously qualitative and quantitative techniques, and is developed in a series of phases, similar to those of clinical drug research, that could be executed in a sequential or iterative manner: a) preclinical or theoretical phase: establishment of theoretical fundamentals and identification of the active components in the evidence base; b) phase I or modelling phase: definition of intervention components, identification of potential barriers to change and of the mechanisms through which interventions should operate; c) phase II or exploratory trial: evaluation of the feasibility and optimisation of the intervention through the execution of quasi-experimental studies; d) phase III or definitive randomised controlled trial, to enable the controlled experimental evaluation of the intervention; e) phase IV or long term implementation phase under real-world conditions. To date, there have been several projects that have successfully applied the MRC framework for the design and evaluation of complex interventions [45]. The conclusions of these studies agree on the usefulness of the MRC framework as a tool for the researchers in the designing, planning and evaluation of innovative interventions to improve health.

In 2006, in order to tackle the problem of integrating health promotion into PHC, the Primary Care Research Unit of the Basque Health Service set up a multidisciplinary team of 12 health professionals: family doctors, paediatricians and nurses in PHC, specialists in preventive medicine, public health, health education, epidemiologists, psychologists and sociologists. Between 2006 and 2007, this group undertook a first preclinical research phase on usefulness of various theoretical models and intervention strategies for health behaviour change (sedentary lifestyle, diet, smoking, alcohol), and identified factors that make their integration in PHC difficult [1]. In line with the conclusions of this work, the objective of the research protocol reported here is the modelling and planning of interventions which are hypothetically feasible and effective for healthy lifestyle promotion in PHC, following four fundamental principles: (1) cooperation between primary care professionals, community partners and researchers, from the design stage; (2) reorganisation of the PCCs in order to facilitate the incorporation of health promotion; (3) adoption of a socio-ecological model, in which the health service plays an important role, complementary to that of other sectors and non-health resources; and (4) use of an appropriate methodological framework for the design and evaluation of complex interventions [1].

## Methods

### Objectives

1) To design innovative programmes for promoting at least two healthy lifestyle behaviours (physical activity, balanced diet, giving up smoking or the moderate consumption of alcoholic drinks), which are hypothetically effective, feasible and sustainable in routine PHC.

2) To evaluate the changes associated with the planning process in the actual healthy lifestyle promotion practice of PHC professionals, attitudes towards prevention and health promotion, and factors associated with the optimisation of such clinical practice.

### Design

A phase I formative research [43] will be performed in four PHC centres of the Basque Health Service – OSAKIDETZA. In a first descriptive stage, a strategic needs assessment will be carried out along with the prioritisation of the areas of preventive practice to be optimised and selection of the aims of the programmes. In a second, creative stage, specific objectives of intervention will be identified based on theoretical models of behaviour change and collaborative design of specific intervention actions for addressing and managing multiple risk behaviours will be undertaken.

Within the formative research, a quasi-experimental pre-post evaluation study will be performed to compare the changes in indicators related to health promotion practice in the four PCCs assigned to the aforementioned formative research process (Intervention Group) and those of other four centres, matched in structural and population characteristics (Control group) [46]. Additionally, Nominal Groups will be performed with professionals belonging to intervention centres, in order to identify the successes, strengths, weaknesses and shortcomings of the process, as well as experiences concerning its usefulness, and difficulties and barriers with respect to the cooperation between researchers and clinicians and between professions within the centres.

The project was approved by the Institutional Primary Care Research Committee of the Basque Health Service/Osakidetza, on 12^th ^April 2007, by the Basque Country Clinical Research Ethics Committee (Ref: 06/2008), and evaluated and approved for funding by the Basque Government Department of Health (Ref: 2007111009).

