### Participants

#### Eligibility criteria

The particular focus of this study, which aims to introduce a process of change in health promotion practice in PHC under a framework of participative research with health professionals, community partners and researchers, determines the two characteristics that define the participants: (1) the intervention unit is the PCC; and (2) the centre must be especially interested in health promotion. The creative work to be undertaken requires that the professionals and health centres be positively motivated with respect to changing risk behaviours of their patients and the integration of health promotion in daily practice. That is why the following factors were considered in order to identify the centres that were eligible: (1) previous history of participation or evaluation of programmes for health promotion in the last 10 years, (2) previous initiatives of preventive practice optimisation and the promotion of healthy lifestyles, (3) existence of programmes, resources, services or initiatives for health promotion in the community or geographical area of reference, (4) positive attitude to working together and cooperation between the professionals of the centre, (5) centres in which it would be possible to make some kinds of changes in the organisation of services, once the potential innovative strategies for approaching multiple risk behaviours have been determined. The commitment of cooperation by a majority plus one of all the professionals of the centre for each of the professions (administrative officers, nurses, family doctors, paediatricians and others) was required to participate in the project.

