#### Recruitment process of the Health Centres and PHC professionals

The identification of the eligible centres was performed via the Medical Directors of the seven divisions of primary care services, under which the PHC of the Basque Health Service – OSAKIDETZA is organised. Four of them accepted to collaborate and they each selected two primary care centres with similar structural and population characteristics. Project presentation sessions were given to the professionals of the selected centres, in which members of the research group explained the scientific and methodological details of the project, and the work plan. Then, each of the professionals were invited to collaborate through the presentation of an informed consent form. The majority of the professionals of each profession agreed to collaborate in eight of the centres; four of them being assigned for convenience to the formative research process, and the other four forming the reference or Control Group. Finally, 130 professionals (82 in the Intervention Group and 48 in the Control Group), collaborated in the project: 46 family doctors (29 in the Intervention and 17 in the Control), 45 nurses (26 in the Intervention and 19 in the Control), 27 administrative officers (18 in the Intervention and 9 in the Control), 10 paediatricians (8 in the Intervention and 2 in the Control), 3 midwives (2 in the Intervention and 1 in the Control group) and 1 social worker (Fig 1).

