**Figure 1 F1:**
[figure not shown]
**Operational organization of the formative process "Prescribe Vida Saludable" in the intervention centres**. **Note**: HC, Health Centre; GP, General Practitioner; Nur, Nurse; Ped, Paediatrician; AS, Administrative Staff; Epi, Epidemiologist; Soc, Sociologist; Psi, Psychologist. Participation in Control health centres, Beraun HC: GP (5), Nur (4), Ped (1), AS (2), Social worker (1); Markina HC: GP (5), Nur (5), AS (3); Berango HC: GP (2), Nur (2), Ped (1), AS (1); and Zurbaran HC: GP (5), Nur (8), AS (3).

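### The controls are described as structurally matched, but the consent rule and the participant counts contradict matching on paediatric and administrative staffing

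*Protocol article*

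**What the plan says.** The Design section sets the intervention centres against "those of other four centres, matched in structural and population characteristics (Control group". The section on recruitment of centres and professionals explains how the centres were found: four medical directors agreed to help and "they each selected two primary care centres with similar structural and population characteristics". Allocation was not random, with "four of them being assigned for convenience to the formative research process".

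Consent had to reach a threshold within each profession. Under Eligibility criteria the requirement is "The commitment of cooperation by a majority plus one of all the professionals of the centre for each of the professions", and paediatricians and administrative officers are named among the professions. The recruitment section reports the outcome in looser terms: "The majority of the professionals of each profession agreed to collaborate in eight of the centres". It then gives the result as "130 professionals (82 in the Intervention Group and 48 in the Control Group), collaborated in the project", with a breakdown by profession.

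The Figure 1 note lists participants for each control centre, for example "Markina HC: GP (5), Nur (5), AS (3", with no paediatrician at that centre. Counts for each intervention centre are in the figure itself, which was not available for this review.

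The Analysis section plans stratified adjustment for confounders, followed by multivariable models built forward from the stratified results.

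**The concern.** The two groups are called similar in structure, yet one supplied 82 participants and the other 48, an average of 20.5 per centre against 12. A majority rule limits how far low participation can explain such a gap, because the number who consented caps the number employed. In two professions the cap on control staff lies below the number of intervention staff who took part.

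With centres assigned by convenience, matching is the main design argument that the change in the control centres shows what would have happened without the programme. If the groups differ in staffing, or in the share of staff who joined, a difference in change over the year may partly reflect those differences. The direction cannot be told from the document: a real effect could be hidden, or a spurious one produced.

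**Working it through.** **Inputs.** Control participants by centre come from the Figure 1 note. Totals by group and profession, and the majority statement, come from the recruitment section. The stricter majority-plus-one rule comes from Eligibility criteria.

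**Reproducing the stated control totals.** Summing the Figure 1 note gives 17 family doctors, 19 nurses, 2 paediatricians, 9 administrative officers and 1 social worker, 48 in all. These agree with the text for the four main professions and for the group total. The text gives the controls a midwife where the note lists a social worker; this does not affect the two professions at issue.

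**Bound on control staff.** If k people consented and they are a majority of the N employed, then k > N/2, so N ≤ 2k − 1. If nobody in a profession consented, the rule can hold only with N = 0. Intervention centres employed at least as many as took part.

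| Profession | Control participants (Beraun, Markina, Berango, Zurbaran) | Most control staff possible | Fewest intervention staff possible |
|---|---|---|---|
| Family doctors | 5, 5, 2, 5 = 17 | 9 + 9 + 3 + 9 = 30 | 29 |
| Nurses | 4, 5, 2, 8 = 19 | 7 + 9 + 3 + 15 = 34 | 26 |
| Paediatricians | 1, 0, 1, 0 = 2 | 1 + 0 + 1 + 0 = 2 | 8 |
| Administrative officers | 2, 3, 1, 3 = 9 | 3 + 5 + 1 + 5 = 14 | 18 |

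Equal staffing is excluded for paediatricians and administrative officers. It is not excluded for family doctors or nurses, who make up 91 of the 130 participants.

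**All staff.** With the social worker, control staff number at most 30 + 34 + 2 + 14 + 1 = 81, or 82 if the midwife is added, against at least 82. Equal totals would need about 48/82 = 59% participation in the controls and 100% in the intervention centres.

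**What equal staffing would require.** With equal staff S in both groups, participation rates stand in the ratio of the counts. For paediatricians S is at least 8, so control participation is at most 2/8 = 25%, a quarter of the intervention rate. For administrative officers it is at most 9/18 = 50%, half the intervention rate. Neither is a majority.

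**Sensitivity.**
- Majority plus one, read literally as N/2 rounded down plus 2 (or everyone, if fewer): administrative officers 2 + 3 + 1 + 3 = 9, family doctors 7 + 7 + 2 + 7 = 23, nurses 5 + 7 + 2 + 13 = 27, paediatricians still 2. Equal numbers of family doctors are then excluded as well (23 against at least 29).
- At least half, which is weaker than either wording: administrative officers 4 + 6 + 2 + 6 = 18, so equality becomes just possible. Paediatricians reach 2 + 0 + 2 + 0 = 4, still below 8.
- Count errors: the intervention counts by profession sum to 29 + 26 + 18 + 8 + 2 = 83, not 82. Removing one person from either group leaves 17 > 14 and 7 > 2.

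**The case against.** The strongest objection is that the bound needs the number who consented, while the article counts those who finally took part. If some control staff signed and then did not join, 2 and 14 are no longer caps. This stands as a condition. The recruitment section uses the same verb for agreeing and for taking part and reports no loss between them, so the reading is natural but not certain. If there was such a loss and staffing was equal, participation differed sharply by group, which also needs reporting.

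Second, structural is not defined and need not mean headcount by profession. Similarity within the pairs chosen by each director cannot be checked without intervention counts by centre. This stands too: the counts contradict matching on two staff groups, not matching as such.

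Third, the analysis compares professionals, and their mix is broadly similar: family doctors 35% against 35%, nurses 31% against 40%, administrative officers 22% against 19%, paediatricians 10% against 4% (chi-square on these four, p = 0.59). Adjustment is planned, and the Evaluation section will examine representativeness and the effect of leavers. This weakens the concern but does not remove it. A test with 10 paediatricians cannot show balance, and forward building does not guarantee that profession enters the model.

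A reader might go further and infer that the groups are not comparable at all, or put a figure on the bias. The document supports neither. The comparison is of change, so staffing differences bias it only if change varies with staffing or participation, and nothing in the article says by how much it would.

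**Conclusion.** The point holds for staffing in two professions. If those who took part are those who consented and the majority rule was met in every centre, the control centres had 2 paediatricians against at least 8, and at most 14 administrative officers against at least 18. The claim of structural matching then cannot extend to these staff. If one of those assumptions fails, either the rule was not met or participation differed sharply between the groups. Each possibility needs a correction or an explanation.

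The paediatric result is robust to how majority is read; the administrative result needs a strict majority. Equal numbers of family doctors and nurses remain possible under a simple majority, as does matching on other structural or population features. The size of any bias in the programme effect cannot be derived from the article.

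**What to change.** 1. In the Design and recruitment sections, name the characteristics on which centres were actually matched and limit the claim to those. State that staffing and participation were not balanced between groups. If staff lists show that staffing was equal, say that participation was not.
2. Report employed, consented and participating staff by centre, profession and group. This separates the three explanations and settles whether participants are the same people as consenters.
3. In the Analysis section, make profession a prespecified fixed term in the models instead of leaving it to forward selection.
4. Add a sensitivity analysis restricted to family doctors and nurses: 29 + 26 = 55 against 17 + 19 = 36.

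Weighting by participation rates is not worth adding, because several control cells hold only 1 to 3 people. A centre-size term would have to be estimated from eight centres.

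The cost is some wording, a table from staff lists and consent forms, a less favourable description of the controls, and slightly wider intervals. For the restricted analysis, with equal variances and people treated as independent, the interval widens by a factor of √[(1/55 + 1/36)/(1/82 + 1/48)] = √(0.0460/0.0330) ≈ 1.18.
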